## Abstract

**Background:**

Central venous catheter-associated bloodstream infections in children are an increasingly recognized serious safety problem worldwide, but are often preventable. Central venous catheter bundles have proved effective to prevent such infections. Successful implementation requires changes in the hospital system as well as in healthcare professionals’ behaviour. The aim of the study is to evaluate process and outcome of implementation of a state-of-the-art central venous catheter insertion and maintenance bundle in a large university children’s hospital.

**Methods/design:**

An interrupted time series design will be used; the study will encompass all children who need a central venous catheter. New state-of-the-art central venous catheter bundles will be developed. The Pronovost-model will guide the implementation process. We developed a tailored multifaceted implementation strategy consisting of reminders, feedback, management support, local opinion leaders, and education. Primary outcome measure is the number of catheter-associated infections per 1000 line-days. The process outcome is degree of adherence to use of these central venous catheter bundles is the secondary outcome. A cost-effectiveness analysis is part of the study. Outcomes will be monitored during three periods: baseline, pre-intervention, and post-intervention for over 48 months.

**Discussion:**

This model-based implementation strategy will reveal the challenges of implementing a hospital-wide safety program. This work will add to the body of knowledge in the field of implementation. We postulate that healthcare workers’ willingness to shift from providing habitual care to state-of-the-art care may reflect the need for consistent care improvement. Trial registration: Dutch trials registry, trial # 3635.

**Trial registration:**

Dutch trials registry (http://www.trialregister.nl), trial # 3635

## Background

Catheter-associated bloodstream infections (CA-BSIs) in hospitals are a worldwide serious persistent problem. Although often preventable, they are a source of morbidity, mortality, prolonged hospital stay, and rising costs [1-4]. CA-BSIs notably occur in units where many patients have central venous catheters (CVC); reported figures range from 1.2 to 23.0 CA-BSIs per 1000 line-days in neonatal intensive care units and from 1.8 to 7.8 CA-BSIs per 1000 line-days in pediatric intensive care units [3-8]. The corresponding figures from a pilot study we performed in 2011 are 11.2 and 7.9. Both unit types admit patients with compromised immune system and patients undergoing invasive procedures [9]. High incidences in neonatal intensive care units may be due to an immature host defence in preterm infants [5,10].

Pronovost et al. showed that the introduction of improved CVC insertion techniques helped to bring down the incidence of CA-BSIs to nearly zero 16 to 18 months later. This study was mainly in adult intensive care units, but the successful outcome encouraged us to improve the CVC care for all children admitted to our children’s hospital [11]. A model developed by Pronovost and colleagues (“Pronovost-model”) will guide the current study protocol [12].

There is growing evidence that a combination of interventions, termed CVC insertion and maintenance bundles, may be effective in preventing CA-BSIs in infants and children as well [9,13-15]. For example by ensuring maximum sterile barrier during CVC insertion and appropriate disinfection during intravenous medication administration. Regrettably, the evidence is limited by differences in the bundle’s insertion components in the various studies [13,16].

Each ward in our children’s hospital tends to have its own habits and protocols with regard to CVC insertion and maintenance care. These protocols are not all in line with the available evidence for optimal CVC care. In addition, the inconsistent policies may confuse patients and their parents upon transfer to another ward. It would be best, therefore, to have one hospital-wide, state-of-the-art CVC insertion and maintenance protocol. Little has been published, however, on successful implementation of large scale innovations like this in a children’s hospital, let alone one guided by the Pronovost-model. The proposed study aims to obtain solid evidence for an effective implementation method. Furthermore, cost-effectiveness of the implementation of a CVC bundle has hardly been addressed, so the question remains whether it provides good value for money. CA-BSIs are known to be associated with high costs. A study in a neonatal intensive care unit in Belgium found that children with CA-BSIs stayed a mean 24 days longer in hospital at a mean extra charge of approximately €12,000 (2). In another study from a pediatric intensive care unit in the USA, the corresponding figures were 9 days and $33,000 (4). Concrete evidence about the potential of a CVC bundle to lower the costs is still lacking however. This study may help enlarge the body of evidence on cost-effectiveness.

The objectives are fourfold: (1) to assess the effects of hospital-wide implementation of a CVC insertion and maintenance bundle on the incidence of CA-BSIs per 1000 line-days over 48 months; (2) to assess adherence to use of the CVC insertion bundle; (3) to assess adherence to use of the maintenance bundle; and (4) to explore the cost-effectiveness of implementing a CVC insertion and maintenance protocol.

### Scientific hypothesis

We will test the following hypothesis: implementation of hospital-wide CVC insertion and maintenance bundles on the guidance of the Pronovost-model promotes protocol adherence and reduces the number of CA-BSIs.

## Methods/design

### Study design

An interrupted times series (ITS) analysis will be performed covering a number of three-month periods in three subsequential phases: pre-intervention, intervention, and post-intervention (Figure 1). The Outbreak Reports and Intervention studies of Nosocomial infection (ORION) statement [17] will be applied to guarantee quality of reporting and the use of appropriate statistical techniques.

**Figure 1 F1:**
[figure not shown]
Interrupted time series study design showing the 48-month timeline of the study, divided into pre-intervention, intervention, and post-intervention stage.

### Setting and participants

The setting of this study is the Erasmus MC-Sophia Children’s Hospital, Rotterdam, the Netherlands. In 2011 it counted 252 beds, 12,403 admissions, and 53,541 patient-days. Distribution over the various wards was as follows: Neonatal intensive care unit: 27 beds, 775 admissions (8,447 patient-days); pediatric intensive care unit: 34 beds (including 6 beds in high dependency transfer unit), 1504 admissions (10,070 patient-days); medium care units: 96 beds, 4,536 admissions (29,436 patient-days); day-care ward, 14 beds, 5,588 admissions (5,588 patient-days); and operation room suite: 8 operation rooms, and 9,207 surgeries. All wards except the day-care ward will be participating in this study.

### Implementation model

Implementation will be guided by the Pronovost-model [12]. The model gives priority to systems operation, centralised support, a collaborative culture, but also promotes local responsibility. Four stages are distinguished: (1) Collect evidence on interventions associated with improved outcomes and select the best feasible ones; (2) Identify possible barriers to implementation by monitoring the current practice and asking stakeholders why they would not comply with current protocols. On the other hand, identify intrinsic and extrinsic motivators that could help implementation; (3) Select process or outcome measures for adherence to the new protocols. Monitoring will encourage healthcare workers’ desired behaviour; (4) All local healthcare workers as much as possible provide care according to the new protocols. Striving to achieve an overall high adherence, implementation will be executed by means of the 'four Es’: 'engage’, 'educate’, 'execute’, and 'evaluate’.

#### ***Collecting evidence***

A state-of-the-art CVC protocol should meet the Centers for Disease Control and Prevention (CDC) recommendations, be in line with leading studies [3,13], and be acceptable for key players in all wards. It must ensure that children who are moved internally always receive the same CVC care. We will set up a working group and a steering committee for this purpose. The working group will first make an inventory of all CVC protocols including port catheters currently used in our children’s hospital. Evidence for effective measures to prevent infections will be retrieved from relevant published studies (Table 1) and assessed on criteria established by the Dutch Institute for Healthcare Improvement CBO in collaboration with the Dutch Cochrane library [18]. The most frequently mentioned measures in these studies are maximum sterile barrier during insertion procedure, site cleaning with chlorhexidine, maximum aseptic administration of intravenous medication, promotion of hand hygiene, and daily evaluation of CVC indication [14,19-22]. Based on the flaws in current practice observed in a pilot study we selected 10 interventions that seemed most appropriate for our patients. The key features are listed in Table 2. In case the literature is inconclusive consensus will be reached through discussion.

**Table 1 T1:** Overview of interventions in and effectiveness of CVC bundles in neonatal intensive care unit and pediatric intensive care unit settings

**Author (year)**	**Setting**	**Design**	**Intervention**	**Reduction of CA**-**BSI**	**Level of evidence**
Wirtschafter et al. (2010)	NICU	A	Proper CVC insertion, hand hygiene promotion, closed tubing system, improved hub care	From 4.32 to 3.22 per 1000 line-days	2-
Sannoh et al. (2010)	NICU	B	Hand hygiene promotion, proper hub care using chloorhexedine with alcohol, glove use promotion, CVC documentation	From 23 to 12 per 1000 line-days*	2++
Bizzarro et al. (2010)	NICU	B	Proper CVC placement, promotion of hand hygiene, daily evaluation CVC need, infection surveillance, dressing replaced on indication	From 8.40 to 1.28 cases per 1000 line-days*	2+
Andersen et al. (2005)	NICU^#^	B	Hand hygiene promotion, maximum barrier during CVC insertion, daily evaluation need for CVC removal	From 21% to 9% (P=0.05, confidence intervals 0.19–1.0)*	2+
Costello et al. (2008)	PICU	C	Hand hygiene promotion, daily evaluation need for CVC removal, CVC insertion kid	From 7.8 to 4.7 and to 2.3 per 1000 line-days	2-
McKee et al. (2008)	PICU	D	Proper insertion and nursing care, empower nurses to stop the insertion procedure if guidelines were not followed, using a checklist to ensure adherence to the guidelines, providing weekly performance feedback, promotion of hand hygiene, chlorhexedine skin preparation,	From 5.2 to 3.0 per 1000 line-days*	2+
Jeffries et al. (2009)	PICU	E	Maximum sterile barrier during CVC insertion, hand hygiene promotion, apply transparent dressing, prepare skin with anti and/ or detergent chlorhexidine gluconate 2%,	From 6.3 to 4.3 per 1000 line-days*	2+
Miller et al. (2010)	PICU	F	Disinfect catheter site using chlorhexedine, maximum barrier, full barrier during pre-packages of the insertion tray, daily assess CVC need, gauze change every 2 days	From 5.4 to 3.1 per 1000 line-days*	2+
Wheeler et al. (2011)	Children’s hospital-wide	D	Full barrier precautions, chlorhexedine skin preparation with 2 minutes scrub and 1 minute air dry, use of insertion checklist, staff empowerment to stop the insertion procedure, daily assess CVC need, promotion of hand hygiene, chlorhexidine-impregnated sponge placed at insertion site, glove use for all CVC manipulations, change dressing every 7 day or on indication earlier, replace tubing sets no more than 72 hour, cap change every 7 day	From 3 to <1 per 1000 line-days*	2+
Chuengchitraks et al. (2010)	PICU	G	Promotion of hand hygiene, maximal barrier precautions, provide skin antiseptic, optimal catheter site selection	From 2.6 to 2.4 per 1000 line-days	2-

Design: A: multi center prospective pre-test posttest study; B: single center prospective pretest and posttest study; C: single center retrospective pretest and prospective posttest group, interrupted time series design; D: single center retrospective pretest and prospective posttest group, time series design; E: multicenter, prospective pretest and posttest group, time series; F: multicenter retrospective pretest and posttest group, interrupted time series; G: single center cohort study; 1++ High-quality meta-analyses, systematic reviews of RCTs, or RCTs with a very low risk of bias; 1+ Well-conducted meta-analyses, systematic reviews of RCTs, or RCTs with a low risk of bias; 1- Meta-analyses, systematic reviews of RCTs, or RCTs with a high risk of bias; 2++ High-quality systematic reviews of case–control or cohort studies, or high-quality case–control or cohort studies with a very low risk of confounding, bias, or chance and a high probability that the relationship is causal; 2+ Well-conducted case–control or cohort studies with a low risk of confounding, bias, or chance and a moderate probability that the relationship is causal; 2- Case–control or cohort studies with a high risk of confounding, bias or chance, and a significant probability that the relationship is not causal; 3 Non-analytic studies; for example, case reports, case series; 4 Expert opinion.

*CVC* central venous catheter, *BSI* bloodstream infection, *NICU* neonatal intensive care unit, *PICU* pediatric critical care unit.

^#^Premature born infants with birth weight < 1500 grams; and *indicate significant reduction of bloodstream infections per 1000 line-days.

**Table 2 T2:** Major components of CVC insertion bundle and maintenance bundle in The Erasmus MC-Sophia Children’s Hospital

**Insertion bundle**	**Components**
Strict hand hygiene according to “my 5 moments”^#^	
Full sterile barrier	Hygienic precaution training for all healthcare workers who insert CVCs
	Sterile gown, mask, hat, double sterile gloves worn by the healthcare worker who inserts the CVC
	Use of pre-packaged CVC insertion kit
	Sterile drape covering the patient for least 80%
Physical barrier between the environment and the child, insertion cart, and healthcare worker who inserts the CVC	
Insertion site cleaned with alcohol 70% with chlorhexidine 0.5% (chlorhexedine 0.2% in water for infants < 26 weeks gestational age)	
Use of a timer displayed at the bedside’s screen to secure an air dry time of at least 30 seconds	
Use a new needle after each attempt to insert a CVC through the intact skin	
Chlorhexedine impregnated sponge attached at insertion site (not in infants < 40 weeks gestational age)	
**Maintenance bundle**	
Strict hand hygiene according to “my 5 moments”^#^	
Hand hygiene	Hand washing when entering the unit, after using the bathroom, and when hands are visually soiled
	Hand disinfection during all other occasions
	Using gloves when risk of contact with body fluids
Catheter site care	Daily inspection of insertion site (e.g. redness, collection of fluids, swelling)
	Change transparent semi permeable dressing on indication only (e.g. loosened, collection of fluids)
Hub care	Disinfection of the hub with alcohol 70% and air dry for at least 30 seconds
	Use of a timer displayed at the bedside’s screen to secure an air dry time of at least 30 seconds
Tubing care	Replace continuous tubing sets every 96 hours, unless visually soiled of contaminated
	Daily replace tube containing lipids, medication, blood or blood products
	Remove intermitted administration sets directly after administration of medication
Daily question whether CVC still needed	

^#^My 5 moments adopted from the CDC [23].

*CVC* central venous catheter.

The working group will prepare a draft protocol for approval by the steering group. This will encompass both the insertion bundle and the maintenance bundle, each with its sub themes. The insertion bundle consists of: preparing a CVC insertion cart and providing assistance to the physician or nurse practitioner during the CVC insertion procedure (e.g. PICC line, umbilical catheter, jugulars/femoralis/subclavia catheter). The maintenance bundle consists of: proper daily nursing care, preparation of intravenous medication, administration of intravenous medication, blood drawing from a CVC, administration of a bacterial-static solution to short bowel patients, removal procedure, port catheter (e.g. general port catheter care, administration of medication and removal of the port needle).

Finally, once accepted the protocol will be made easily accessible at our in-hospital Intranet through keywords enabling to navigate to all sub themes. In addition we will write a CVC infection prevention manual with special attention to infection prevention in sick children and the side effects of BSIs. It will also present evidence from the literature on preventive interventions.

#### ***Barriers***

We have already explored barriers to successful implementation of the selected interventions. In five in-depth semi structured interviews with physicians and nurses we discussed the key elements of the CVC procedures that would have to be changed – and at the same time elicited potential barriers. Nurses as well as physicians said that applying an air dry time of 30 seconds after disinfection of the skin or needless connector was time-consuming. Physicians in addition doubted the necessity to use a new needle after failed attempts to insert a CVC through the skin.

#### ***Measuring***

The outcome measure is the number of CA-BSIs per 1000 line-days, calculated by dividing the number of bloodstream infections by the risk-adjusted denominator 1000 line-days. As a baseline measurement we prospectively collected data from 1st January 2011 to 1st January 2012. Over that period the number of CA-BSIs per 1000 line-days was 11.2 at the neonatal intensive care unit and 7.9 at the pediatric intensive care unit.

As secondary outcome (process measures) we selected degree of adherence to safety procedures, e.g. maximum sterile barrier during the CVC insertion procedure and adherence to hygienic protocols during intravenous administration. Adherence will be documented with the use of two observation tools (Tables 3 and 4). Performance related to the insertion procedure will be measured with two tools: use of the time out procedure that is linked with the CVC insertion protocol (Additional file 1: Table S1) and a questionnaire daily popping up in the patient’s electronic record informing after signs of infection at insertion site as well as the need of having the CVC in place.

**Table 3 T3:** Process indicators CVC insertion monitoring form

	**Process indicator**	**Satisfied**
1	Skin cleaned with alcohol 70% with chlorhexidine 0.2%; or chlorhexidine 0.2% in water in infants with a gestational age < 26 weeks	Yes O No O
2	Air dry of at least 30 seconds after skin preparation prior to guide-wire insertion	Yes O No O
3	New needle used after each attempt to insert a CVC through the intact skin	Yes O No O
4	Sterile drape covering the patient for least 80%	Yes O No O
5	The provider inserting the CVC used maximum sterile barrier e.g. sterile gown, double sterile gloves, mask, and hat	Yes O No O
6	Optimal insertion site was selected or another site was argued for	Yes O No O
7	Echo use during insertion of jugularis and subclavia catheter	Yes O No O
8	Chlorhexidine impregnated sponge used in infants < 40 weeks gestational age	Yes O No O

*CVC* central venous catheter.

**Table 4 T4:** Process indicators CVC nursing care monitoring form

	**Process indicator**	**Satisfied**
1	Appropriate hand hygiene prior to preparation of intravenous medication	Yes O No O
2	Disinfection of the cap or ampoule’s surface using alcohol 70%	Yes O No O
3	Applying 30 seconds air drying time after disinfection ampoule’s surface	Yes O No O
4	Disinfection of connector with alcohol 70%^#^	Yes O No O
5	Or disinfection of the stop cock in case intravenous medication is administered using an extension-line applying alcohol 70%^#^	Yes O No O
6	Applying 30 seconds air dry time for the stop cock of connector	Yes O No O
7	Daily question whether the CVC is still needed in PDMS	Yes O No O
8	Daily check of the insertion place for inflammation	Yes O No O
9	Aspirated blood from the CVC will not be returned to the patient	Yes O No O
10	The blue side of the Biopatch is visible	Yes O No O

*CVC* central venous catheter, *PDMS* patient data management system.

^#^select one depending on the mode of administration.

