#### ***Implementation strategies***

*Engage*. We will inform all stakeholders and senior management staff about the current high number of CA-BSIs per 1000 line-days and the need to reduce this number, and address the undesirability of having different CVC protocols in place – implying we need to implement general preventive measures hospital-wide. Representative stakeholders from all wards will be invited to join the steering committee. Final approval of the CVC protocol by the steering committee is required and the members will support implementation in their respective wards and operation room suite.

Table 5 provides an overview of proposed implementation strategies. Strategies for the dissemination of knowledge are based on the Pronovost-model and others [12,24,25].

**Table 5 T5:** Selected implementation strategies

**Intervention types**	**Components**
Education program, theme week	Multidisciplinary seminar
	Workshop for physicians
	Instruction for nurses
	Instruction on hygienic insertion and maintenance
Reminders	Leaflets
	Screen savers
	Daily questionnaire CVC need, pop-up in electronic patient management system
	Sticker attached at disinfection solution: apply 30 seconds air dry time
Feedback (quarterly)	Reporting incidence of CA-BSI
	Reporting adherence to insertion bundle
	Reporting adherence to maintenance bundle
Engagement of the managing staff	One-liners combined with picture
Awareness	Time out procedure, and staff empowerment to stop in case of protocol violation
	Daily goal sheet
Procedures	Revised protocols
	CVC infection preventions manual.
	Timers
	30 seconds air dry timer displayed on bedside screen

*CA-BSI* catheter-associated bloodstream infection, *CVC* central venous catheter.

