### Secondary outcomes

Rate of adherence to the CVC insertion bundle and rate of adherence to the maintenance bundle will serve as secondary outcomes.

The attending nurse will assess adherence to the CVC insertion bundle during the insertion procedure (Table 3). To this aim we designed a digital tab with drop-down menu for the two different patient data management systems. The time out procedure prior to the CVC insertion is predominantly added for creating safety awareness during insertion (Additional file 1: Table S1). During the insertion procedure all involved healthcare workers are encouraged to make comments and to stop the procedure in case of violation of insertion bundle. Intravenous medication preparation and administration items will serve to measure adherence to the CVC maintenance bundle (Table 4). Purpose-trained nurses will randomly assess these items during planned daily care.

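### The insertion adherence form (Table 3) does not match the insertion bundle (Table 2): no hand-hygiene item, two items from outside the list, and only Yes/No where an item may not apply

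*Protocol article*

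**What the plan says.** The Secondary outcomes section states: "Rate of adherence to the CVC insertion bundle and rate of adherence to the maintenance bundle will serve as secondary outcomes". The Measuring section names Tables 3 and 4 as the observation tools that document adherence.

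Table 2 lists the major components of each bundle. Its insertion part opens with "Strict hand hygiene according to" the five-moments scheme. The text below Table 2 gives the procedures in scope: "e.g. PICC line, umbilical catheter, jugulars/femoralis/subclavia catheter".

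Table 3 has eight insertion items, each with a Yes and a No box. Among them are "New needle used after each attempt to insert a CVC through the intact skin" (item 3), an item on choice of insertion site (item 6), "Echo use during insertion of jugularis and subclavia catheter" (item 7) and an item on the impregnated sponge in one age group (item 8).

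Table 4, the nursing-care form, has ten Yes/No items. A footnote tells the observer to choose between items 4 and 5 according to the mode of administration. Item 7 is "Daily question whether the CVC is still needed in PDMS". Table 2 lists the daily question as a maintenance component, and Table 5 also lists it among the reminders: "Daily questionnaire CVC need, pop-up in electronic patient management system".

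The Sample size section gives insertion adherence of 60% at baseline and 100% as the aim, with 15 insertion observations per period.

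**The concern.** A bundle adherence rate should rise and fall with delivery of the bundle. With Table 3 as printed, an insertion done without hand hygiene can score full marks. An insertion that meets every Table 2 component can lose marks on site choice or echo. Where an item cannot apply, the observer has to tick a box anyway, and nothing in the protocol says which one. Two observers can then score the same insertion differently, and a change in the mix of catheter types between periods can look like a change in behaviour.

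The rate is part of the study hypothesis, is compared between periods, and is fed back to the wards every quarter. With only 15 insertions per period, a few miscoded forms are enough to distort it.

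**Working it through.** **Step 1. Set Table 3 against the Table 2 insertion list.**

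| Table 3 item | In Table 2 insertion list? | Applies to every insertion? |
|---|---|---|
| 1 Skin cleaning | Yes, but the alcohol solution has chlorhexidine 0.2% here and 0.5% in Table 2 | Yes |
| 2 Air drying, 30 seconds | Yes (through the timer) | Yes |
| 3 New needle | Yes | No: nothing to score if the first attempt succeeds |
| 4 Drape, 80% | Yes | Yes |
| 5 Maximum sterile barrier | Yes | Yes |
| 6 Site selection | No | Yes |
| 7 Echo | No | No: jugular and subclavian lines only |
| 8 Sponge | Yes, with the opposite age condition | No: one age group |

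Counts: items outside Table 2, 2/8 = 25%; conditional items without a not-applicable box, 3/8; hand-hygiene items, 0. Table 4 does have a hand-hygiene item (item 1), so this gap is specific to the insertion form.

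On Table 4, items 9 (aspirated blood) and 10 (sponge visible) are also conditional. Only items 4 and 5 have a provision for this.

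**Step 2. Reproduce the plan's 15 insertion observations.** Inputs from the Sample size section: p1 = 0.60, p2 = 1.00, alpha 0.05 (taken as two-sided), power 0.80. With pooled variance and p̄ = 0.80:

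n = [1.96·√(2·0.80·0.20) + 0.8416·√(0.60·0.40 + 1.00·0)]² / 0.40² = (1.109 + 0.412)² / 0.16 = 14.5, so 15 per period. Power at n = 15 is 0.816. The plan's figure reproduces.

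**Step 3. What an inapplicable item could do.** The protocol states neither a scoring rule nor the catheter mix. For illustration only, assume all-or-none scoring, and assume that a share q of insertions has an inapplicable item that is ticked No. The reachable rates are then 0.6(1 − q) before and (1 − q) after. The same formula gives:

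| q | Before | After | n needed per period | Power at n = 15 |
|---|---|---|---|---|
| 0 | 60% | 100% | 15 | 0.82 |
| 0.1 | 54% | 90% | 24 | 0.60 |
| 0.2 | 48% | 80% | 35 | 0.44 |
| 0.3 | 42% | 70% | 49 | 0.33 |

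For any q above zero the 100% target cannot be reached; one such line among 15 already gives 14/15 = 93%. Under the same rule, with true adherence unchanged at 60%, a shift in q from 0.1 to 0.3 between periods would move the rate from 54% to 42%. That is 12 points with no change in behaviour.

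If items were averaged instead, one inapplicable item ticked No would limit that insertion to 7/8 = 87.5%. If observers ticked Yes there would be no cap, but the item would be scored as met when there was nothing to meet. The result therefore depends on the coding convention.

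**The case against.** The strongest reply has four parts.

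- **Table 2 claims only major components.** Site selection and echo could belong to the full insertion protocol, and items 1 to 5 do correspond to Table 2 entries. This stands, and it limits the conclusion. A reader might infer that the rates do not measure bundle adherence at all, but the document does not support that. It supports incomplete coverage with two items from outside the list. The reply does not explain why the first listed component is absent.
- **The working tools are not shown.** The insertion form is run as a digital tab with a drop-down menu, observers use a structured case report form, and the time-out form is in an additional file. Any of these might hold a hand-hygiene item or a not-applicable option. That is possible and would soften the point. Yet Tables 3 and 4 are what the Measuring section names as the tools, and they should be right as printed.
- **Inapplicable items need not be ticked No.** Item 7 is worded conditionally, item 3 can be ticked Yes after one attempt, and a 100% target suggests that the authors did not mean such items to count as failures. This is fair, and is why Step 3 is only an illustration.
- **The daily question belongs to the bundle.** Because Table 5 lists the pop-up as a reminder, a reader might infer that Table 4 item 7 scores something outside the bundle and was unmet before roll-out by construction. Table 2 lists it as a maintenance component, and no baseline for it is given. Nor is it stated that display of the pop-up alone counts as satisfied. A jump from 0 to 1 would add 1/9 = 11 points to an item average, but that figure rests on assumptions. Under an all-items rule, item 7 at zero would make baseline maintenance adherence 0%, against the stated 20%.

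Nor does the Secondary outcomes section confine the maintenance measure to medication items. It says that those items will serve, and cites Table 4 as a whole.

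**Conclusion.** The point holds for the insertion form. As printed, Table 3 omits the first listed insertion component, includes two items that Table 2 does not list, and gives no way to record that items 3, 7 or 8 do not apply. The insertion adherence rate is therefore an incomplete measure of the bundle, and it can vary with catheter mix and coding.

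The mismatch itself follows from comparing the tables and needs no assumption. Its numerical effect cannot be fixed from the protocol. The unreachable 100% target and the loss of power hold only if inapplicable items are ticked No and scoring is all-or-none.

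For the maintenance form the point is narrower. Some conditional items lack a not-applicable option, and item 7 is both a bundle component and an implementation reminder. That is a reason to show it separately as well, not to remove it.

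The same comparison exposes two direct contradictions between Tables 2 and 3: the chlorhexidine concentration in item 1 and the age condition in item 8. These passages must be reconciled; which is right is not judged here.

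This concerns a secondary outcome. It should be corrected, because the remedy is cheap and the rate is both tested and fed back.

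**What to change.** 1. Add a hand-hygiene item to Table 3.
2. Add a not-applicable option to the conditional items on both forms (Table 3 items 3, 7 and 8; Table 4 items 9 and 10), and score each observation over its applicable items.
3. Report site selection and echo separately from the insertion bundle rate, or list them in Table 2 as components.
4. Keep Table 4 items 7 and 8 in the maintenance rate, since the daily question and daily site inspection are listed components. Also show item 7 on its own, because the pop-up is itself a reminder under Table 5.
5. While revising, reconcile Table 3 items 1 and 8 with Table 2.

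The cost is a small edit to the forms, the drop-down tab and the scoring rule. The downside is that any insertions observed before the change would lack the hand-hygiene item. For comparisons that include those periods, hand hygiene would have to be reported separately. The protocol does not say that Table 3 was already in use in 2011; it calls the baseline adherence rates estimated, so the extent of this loss is unknown.
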